### Criteria for eligibility of participating centers

The surgeons, endocrinologists, radiologists, and nuclear medicine physicians participating in this clinical trial are practitioners exercising medicine in either a university hospital or a comprehensive cancer center in France that belongs to the ENDOCAN-TuThyRef network, a network for treatment of thyroid cancer sponsored and financed by the French National Cancer Institute. All participants have expertise in treating thyroid cancer. Furthermore, the participating surgeons routinely perform complete central neck dissections and were chosen to participate in this study due to a homogenous technique among these surgeons [53].

### Who will take informed consent?

Prior to registration in the trial, written informed consent is obtained from the patient during a consultation. The surgeon, endocrinologist, or nuclear medicine physician informs the patient and obtains their informed consent. Two identical consent forms are signed with one of the original forms retained by the patient, the other retained by the investigators. The patient information and consent form can be found in Annex 1. Additional informed written consent is obtained at the same time for use of biological specimens for research, in accordance with the articles L1211-1 to 9 of the French Public Health Code.

## Interventions

### Explanation for the choice of comparators

The primary objective of this study is to assess the non-inferiority of total thyroidectomy alone as compared to total thyroidectomy with bilateral prophylactic central compartment neck dissection in terms of the rate of complete remission (excellent response) at 1 year after randomization, for differentiated thyroid cancer cT1bT2N0.

Group 1 (reference group): total thyroidectomy with bilateral prophylactic central compartment (level VI) neck dissection as defined by the American Thyroid Association [38]. This is a standard treatment recognized by the French Society of Otolaryngology Head and Neck Surgery [15]. The number of lymph nodes resected, the number of metastatic nodes, their size, and the presence or absence of extranodal spread will be recorded. Due to the large natural variability of the number of lymph nodes retrieved in a PND, [53] no patient will be excluded on the basis of number of lymph nodes.

Group 2 (“experimental” group): total thyroidectomy alone without neck dissection. This is recognized as a standard treatment by the Francophone Association of Endocrine Surgery [19].

### Intervention description

#### Randomization of patients

*Pre-registration (inclusion)* of eligible patients after signed informed consent.Surgery must be performed within 4 months of pre-registration.Quality of life (SF-36, EQ-5D, STAI) questionnaires will be completed by the patient within 1 month before the surgery.Before surgery, the patients will first be pre-registered (included) to check that the thyroid nodule is classified cT1bT2N0 and the FNAB cytology is classified type 5 or 6 according Bethesda (Appendix 2).Randomization (and validation of the inclusion)

Randomization (and validation of the inclusion) will then be performed:Before surgery for patients with malignant cytology (Bethesda 6)OR in the operating room, after total thyroidectomy without any particular dissection of paratracheal spaces and after confirmation of malignancy by intra-operative frozen section analysis for patients with suspicious cytology (Bethesda 5).

For patients with a nodule Bethesda 5, the randomization form will incude a confirmation of malignancy of the intra-operative frozen section analysis for patients with suspicious cytology Figs. 1 and 2.

**Fig. 1 Fig1:**
[figure not shown]
Diagram of the trial design

**Fig. 2 Fig2:**
[figure not shown]
Diagram of randomization

#### Treatments

##### Baseline assessment

Inclusion and non-inclusion criteria and patient consentNeck ultrasoundLaryngoscopySerum calciumEQ-5D 3 Levels (Annex 2) [48]Quality of life (SF-36) (Annex 3) [47]Anxiety (State-Trait Anxiety Inventory) (Annex 4) [49]Subjective dysphonia and dysphagia (measured via the Voice Handicap Index (ANNEX 5) [45] and SWAL-QOL) (Annex 6)[46]

##### Surgery

Group 1 (reference group): total thyroidectomy with bilateral prophylactic central compartment neck dissectionGroup 2 (“experimental” group): total thyroidectomy alone without neck dissection.

##### Radioactive iodine

All patients will have Tg/LT4 measured 8 +/− 2 weeks postoperatively, before stimulation with recombinant human thyrotropin (rhTSH).

Then, for all patients (whichever the group), radioactive iodine will be administered after 2 months but within 4 months postoperatively: 30 mCi (1.1 GBq) ^131^I after stimulation with human recombinant thyrotropin (rhTSH)

A ß-HCG test (serum or urine) will be performed before any radioiodine administration.

##### Follow-up

All patients will have a postoperative visit within 4 months of the surgery with the surgeon to record post-op complications.

For all patients, Tg/LT4 and anti-Tg antibodies (anti-Tg Ab) measured 8 +/−2 weeks postoperatively, before stimulation with recombinant human thyrotropin (rhTSH).

At 8 +/− 2 weeks post-op before 131I:-Quality of life (SF-36) [47]-EQ-5D 3 Levels [48]-Anxiety (State-Trait Anxiety Inventory) [49]-Subjective dysphagia (measured via the SWAL-QOL questionnaire) [46]

For all patients (after 2 months but within 4 months postoperatively at the time of 131I administration:Stimulated usTg (Tg/rhTSH), anti-Tg antibodies (anti-Tg Ab)Neck ultrasoundWhole body scintiscan with SPECT performed 2–5 days after the RAI administrationQuality control of total thyroidectomy will be ensured by calculation of the % of 131I uptake, as an estimate of the size of thyroid remnant.

Further follow-up consists in:1 year after surgery (8 +/− 2 months after 131I) (primary endpoint): usTg on thyroxine treatment (usTg/LT4) with a standard ultrasensitive kit, anti-Tg Ab, neck ultrasoundYearly for 5 years (+/− 2 months after 131I): Tg/LT4, anti-Tg Ab, neck ultrasoundIf suspicious lesion (according to standardized criteria on ultrasound [52] > or = 8 mm (smallest dimension): indication for cytological examination by fine-needle aspiration biopsy (FNAB) and, for lymph nodes, for a determination the of level of thyroglobulin (Tg) in the needle washout fluidIf a suspicious lesion <8mm is visualized on ultrasound (according to standardized criteria,[52] cytology with FNAB (and Tg in the needle washout fluid) will be performed upon decision of the center’s principal investigators

Functional evaluation and quality of life:Immediate postoperative complications (0–4 months after surgery) (hypoparathyroidism requiring supplementation, recurrent nerve paralysis visualized on systematic laryngoscopy)Complications at 1 year: treatment for persistent hypoparathyroidism, recurrent nerve paralysis visualized on systematic laryngoscopy performed at 1 yearAt 1 year after randomization: Subjective dysphonia (measured via the Voice Handicap Index [45]), Subjective dysphagia (measured via the SWAL-QOL questionnaire [46])Complete remission at 1, 3, and 5 years after randomizationAt 1, 3, and 5 years after randomization: Quality of life [SF-36 + EQ-5D], Anxiety (State-Trait Anxiety Inventory), all questionnaires in their validated French translation:Quality of life (SF-36) [47]EQ-5D 3 Levels [48]Anxiety (State-Trait Anxiety Inventory) [49]Subjective dysphonia (measured via the Voice Handicap Index, VHI) [45]Subjective dysphagia (measured via the SWAL-QOL questionnaire) [46]

##### Translational research

BRAF V600E mutational analysis will be performed on all primary tumors (corresponding to the surgical specimen recovered during the thyroidectomy) on formalin-fixed paraffin-embedded (FFPE) blocks or slides as a separate study not included herin.

### Criteria for discontinuing or modifying allocated interventions

Secondary exclusion will be performed for patients in whom final pathology (non-frozen section analysis but defintive pathological evaluation) does not confirm the presence of a differentiated thyroid cancer.

In no other instances does this study provide for discontinuing or modifying allocated interventions.

Reasons for withdrawal from the trial (study interventions and follow-up) may include:Lost to follow-upWithdrawal of consentDeath

If a patient does not return for a scheduled visit, every effort will be made to contact them. In any case, every effort will be made to document the patient outcome and all attemps should be documented in the corresponding medical file. The investigator will inquire about the reason for withdrawal, request the patient to return for a final visit, if applicable, and follow up with the patient regarding any unresolved adverse events. The early termination final visit should include all assessments listed for the End of Study visit.

If the patient withdraws their consent for the study, no further study-specific evaluations will be performed, and no additional data will be collected. The sponsor may retain and continue to use any data and samples collected before such refusal except in case of patient opposition. Any opposition will be transmitted by the investigator to the sponsor without undue delay.

### Strategies to improve adherence to interventions

Locally in each center, follow-up visits will be programmed in advance and patients informed in advance of the follow-up program.

### Relevant concomitant care permitted or prohibited during the trial

Pregnancy is to be avoided before and for 6 months following the administration of ^131^I. Patients are counselled to use a method of contraception.

### Provisions for post-trial care

Patients will be followed as part of this clinical trial for a maximum of 5 years. After that period, routine follow-up as standard of care will be performed.

### SPIRIT Reporting guidelines

In this report, we have used the SPIRIT reporting guidelines [54].

### Outcomes: Primary criterion

The primary criterion is the rate of patients *in complete remission (excellent response) at 1 year after radomization* as defined by the presence of the 3 criteria:Normal whole body scan (SPECT-CT) at the time of administration of ^131^I [SPECT-CT will be performed 2–5 days after the administration of 30 mCi (1.1 GBq) of ^131^I after stimulation using injected recombinant human TSH (rhTSH)],Normal neck ultrasound at 8+/−2 months after ^131^I administrationUnstimultaed ultrasensitive thyroglobuline while on L-thyroxine treatment (usTg/LT4) ≤ 0.2 ng/mL without anti-Tg antibodies (TgAb) at 8+/−2 months after ^131^I administration

### Outcomes: Secondary criteria

#### Oncologic secondary criteria

Thyroglobulin levels after surgery alone (ultrasentive thyroglobuliin, usTg/T4) measured while on T4 treatment, 8 +/−2 weeks postoperatively, before stimulation or administration of radioactive iodinePercent of patients in complete remission (excellent response) at 3 and 5 years after randomization, as defined by negative imaging and either unstimultaed ultrasensitive thyroglobulin while on L-thyroxine treatment (usTg/LT4) ≤ 0.2 ng/mL) without anti-Tg antibodies (TgAb) or TSH-stimulated Tg<1ng/mL

The endpoint of 5 years reflects the data from a prospective multicenter study of 715 patients [Brassard M et al J Clin Endocrinol Metab 2011] reporting that 81% of recurrences occurred within 5 years, and from a retrospective study of 1020 patients followed for 10 years [Durante C et al J Clin Endocrinol Metab 2013] reporting that all structural recurrences occurred within 8 years, with 77% occurring within 5 years.Percent of patients at 1, 3, and 5 years after randomization with structural incomplete response in the neck defined by the presence of structural or functional evidence of disease, with any Tg level, with or without anti-Tg antibodiesPercent of patients at 1, 3, and 5 years after randomization with biological incomplete response defined by negative imaging and suppressed Tg ≥1 ng/mL or stimulated Tg≥10ng/mL or rising anti-Tg antibody levelsPercent of patients at 1, 3, and 5 years after randomization with an indeterminate response defined by nonspecific findings on imaging studies and/or faint uptake in thyroid bed on RAI scanning (if performed) and/or on stimulated Tg detectable but <1ng/mL and/or stable or declining TgAb in the absence of structural or functional diseasePercent of patients at 1, 3, and 5 years after randomization with diagnosis of distant metastases on metabolic imaging (^131^I, ^18^FDG-TEP) or cross-sectional imaging, and confirmed cytologically (except for metastases with ^131^I uptake) or with repeat imaging at 6 months (if cytology not possible).Percent of patients at 1, 3, and 5 years after randomization having undergone further treatment (surgery or 2nd therapeutic administration of 131I, number of retreatments per patient and indication for each retreatment)

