#### Secondary objectives

To compare total thyroidectomy and radioactive iodine (^131^I) to total thyroidectomy with bilateral prophylactic central compartment neck dissection and 131I in terms of:Thyroglobulin levels after surgery alone (usTg/T4) measured while on T4 treatment, 8+/−2 weeks postoperatively, before stimulation and administration of radioactive iodinePercent of patients in complete remission (excellent response) at 3 and 5 years after randomization, as defined by a normal neck ultrasound and usTg/LT4 ≤ 0.2 ng/m. The endpoint of 5 years reflects the data from a prospective multicenter study of 715 patients reporting that 81% of recurrences occurred within 5 years,[43] and from a retrospective study of 1020 patients followed for 10 years reporting that all structural recurrences occurred within 8 years, with 77% occurring within 5 years [44].Percent of patients at 1, 3, and 5 years after randomization with structural incomplete response in the neck defined by a malignant lesion in the neck detected by ultrasound and confirmed by cytology (and/or Tg in the needle washout fluid >10ng/ml). Cytology will be mandatory for suspicious lesions measuring 8mm or more in the smallest diameter; lesions with suspicious features on ultrasound but measuring <8 mm may undergo cytology at the discretion of the center’s principal investigators.Percent of patients at 1, 3, and 5 years after randomization with biological incomplete response defined by a normal neck ultrasound and absence of disease detected on other conventional or metabolic imaging (^131^I, ^18^FDG-TEP), if performed, associated with a serum Tg/LT4>0.2 ng/mlPercent of patients at 1, 3, and 5 years after randomization with an indeterminate response defined by a suspicious lesion on neck ultrasound without cytological proof of disease and/or detection of TgAbPercent of patients at 1, 3, and 5 years after randomization with diagnosis of distant metastases on metabolic imaging (^131^I, ^18^FDG-TEP) or cross-sectional imaging, and confirmed cytologically (except for metastases with ^131^I uptake) or with repeat imaging at 6 months (if cytology not possible)Percent of patients at 1, 3, and 5 years after randomization having undergone further treatment (surgery or 2nd therapeutic administration of ^131^I, number of retreatments per patient and indication for each retreatment)At 1 year: percent of patients with persistent hypoparathyroidism with supplementation and/or persistent vocal fold paralysis; subjective dysphonia (Voice Handicap Index)[45] and dysphagia (SWAL-QOL)[46] (questionnaires in their validated French versions) compared between groups after randomization: Quality of life SF36[47], EuroQol EQ-5D,[48] Anxiety (State-Trait Anxiety Inventory-STAI)[49]Cost-utility analysis.

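### The secondary response categories are defined in two incompatible ways, under Secondary objectives and under Oncologic secondary criteria; the 1-year primary endpoint is not affected

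*Protocol article*

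**What the plan says.** The protocol article gives two lists of the same secondary oncologic endpoints, one under Secondary objectives and one under Oncologic secondary criteria.

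- **Excellent response at 3 and 5 years.** Secondary objectives: "as defined by a normal neck ultrasound and usTg/LT4 ≤ 0.2 ng/m", with no antibody condition. Oncologic secondary criteria: negative imaging plus either the same unstimulated cut-off "without anti-Tg antibodies (TgAb) or TSH-stimulated Tg<1ng/mL".
- **Biological incomplete response at 1, 3 and 5 years.** Secondary objectives: clear imaging with Tg on L-thyroxine above 0.2 ng/mL. Oncologic secondary criteria: "biological incomplete response defined by negative imaging and suppressed Tg ≥1 ng/mL or stimulated Tg≥10ng/mL", or rising antibodies.
- **Structural incomplete response at 1, 3 and 5 years.** Secondary objectives: "structural incomplete response in the neck defined by a malignant lesion in the neck detected by ultrasound and confirmed by cytology" and/or by a washout Tg above 10 ng/mL. Oncologic secondary criteria: "structural incomplete response in the neck defined by the presence of structural or functional evidence of disease, with any Tg level".
- **Indeterminate response at 1, 3 and 5 years.** Secondary objectives: a suspicious ultrasound lesion without cytological proof, and/or any detected antibodies. Oncologic secondary criteria: non-specific imaging, faint thyroid-bed uptake, "and/or on stimulated Tg detectable but <1ng/mL and/or stable or declining TgAb".

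Neither list gives an order of precedence. The statistical methods for secondary outcomes plan a separate chi-square test for each type of response.

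The primary endpoint reads the same under Primary objective and under Outcomes: Primary criterion. Both require normal SPECT-CT, normal ultrasound and unstimulated Tg "≤ 0.2 ng/mL without anti-Tg antibodies (TgAb) at 8+/−2 months after ^131^I administration".

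**The concern.** Two lists of the same endpoints at the same time points should give the same answer for the same patient. Here all four definitions differ, and nothing else in the article says which list governs. Because the categories are tested one by one, a patient who moves between lists changes the numerator of one or more tests, and a patient who fits two categories is counted in both.

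These endpoints carry the oncologic comparison after 1 year, when the primary endpoint is no longer measured. The trial is open-label and accrual began in August 2018. Follow-up data are therefore accumulating while the definitions remain unsettled in the published text.

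**Working it through.** The article states no figure to reproduce, so the check applies both sets of rules to the same patients.

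**Inputs.** The definitions come from Secondary objectives and Oncologic secondary criteria. The test schedule comes from Follow-up: unstimulated Tg, antibodies and ultrasound at 1 year and then yearly, with stimulated Tg scheduled only at radioiodine administration.

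**Single profiles (3- and 5-year rules for excellent response)**

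| Profile | Secondary objectives | Oncologic secondary criteria, as printed |
|---|---|---|
| Negative imaging, usTg 0.5, no antibodies | biological incomplete | no category |
| Negative imaging, usTg 0.1, stable antibodies | excellent and indeterminate | indeterminate |
| Negative imaging, usTg 0.1, rising antibodies | excellent and indeterminate | biological incomplete |
| Negative imaging, usTg 1.5, stable antibodies | biological incomplete and indeterminate | biological incomplete and indeterminate |
| Negative imaging, usTg 0.1, stimulated Tg 0.5, no antibodies | excellent | excellent and indeterminate |
| Suspicious lesion, not biopsied | indeterminate | indeterminate, or structural if read as evidence of disease |

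**Grid on scheduled tests only.** Crossing 3 imaging results (negative, suspicious without cytology, proven malignant), 3 values of usTg (0.1, 0.5, 1.5) and 3 antibody states (none, stable, rising) gives 3 × 3 × 3 = 27 profiles.

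- Classified differently by the two sections: 6 of 9 with negative imaging, 0 of 9 with a suspicious lesion and 6 of 9 with proven malignancy, so 6 + 0 + 6 = 12 of 27.
- In two categories at once: 12 of 27 under Secondary objectives and 1 of 27 under Oncologic secondary criteria.
- In no category: 0 of 27 and 1 of 27 respectively.

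The grid treats an unproven suspicious lesion as non-specific imaging under Oncologic secondary criteria. It therefore understates the structural difference.

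**If "and/or on stimulated Tg detectable but <1ng/mL and/or stable or declining TgAb" was meant to read non-stimulated.** The first profile becomes indeterminate under Oncologic secondary criteria and is still biological incomplete under Secondary objectives. Negative imaging with usTg 0.5 and rising antibodies now agrees, which leaves 12 − 1 = 11 differing profiles if 0.1 counts as undetectable. If 0.1 is detectable, negative imaging with no antibodies becomes both excellent and indeterminate under Oncologic secondary criteria, giving 11 + 1 = 12.

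**Stimulated routes.** The alternative "or TSH-stimulated Tg<1ng/mL" and the stimulated Tg limit of 10 ng/mL can apply at 1, 3 and 5 years only to patients who had an unscheduled stimulation test.

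**The case against.** The strongest reply is that the list under Secondary objectives is loose wording and the analysis plan, which is not shown, will fix the derivation. Precedence between categories is ordinary analysis-plan content. The data analyst is also to be blinded to group, which limits data-driven choice. This narrows the risk, but two cut-offs for one endpoint are a contradiction, not an omission: an analysis plan that follows one list departs from the other.

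Some narrower replies stand in part.

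- Secondary objectives classes any detected antibodies as indeterminate, so antibody-positive patients were probably not meant to count as excellent. Without a precedence rule the text still lets them count as both.
- The primary analysis population excludes patients with detectable antibodies. If the secondary analyses use that population too, the antibody examples largely drop out. The article does not say so, and the first profile in the table does not depend on antibodies.
- Part of the overlap and the gap under Oncologic secondary criteria rests on a probable misprint of non-stimulated. The disagreement between sections remains under either reading.

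A reader might infer stronger claims, which the document does not support.

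- **Every patient with unstimulated Tg between 0.2 and 1 and normal imaging moves.** With rising antibodies the patient is biological incomplete under both sections. With stable antibodies the patient is indeterminate under both, although Secondary objectives adds a second category.
- **Most biochemical failures move.** The cited remission rates of 94% and 90.2% would give (1 − 0.94) × 598 ≈ 36 to (1 − 0.902) × 598 ≈ 59 failures at 1 year. These include imaging failures, and no Tg distribution is given.
- **The primary endpoint is ambiguous.** It is not.
- **Reconciliation would make 3- and 5-year excellent response identical to the primary endpoint.** It would not, because the primary also requires the post-radioiodine scan, which is not scheduled at 3 or 5 years.

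**Conclusion.** The point holds for the secondary response categories only: excellent response at 3 and 5 years, and structural incomplete, biological incomplete and indeterminate response at 1, 3 and 5 years. The two sections contradict each other on all four, and the reported rates and between-group comparisons depend on which is followed. The clearest case is normal imaging with unstimulated Tg above 0.2 and below 1 ng/mL and no antibodies.

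The 12 of 27 profiles describe combinations of findings, not expected patients. The number of patients affected cannot be estimated from the document. The conclusion rests on the definitions as printed, and it survives reading the doubtful phrase as non-stimulated. It does not touch the primary endpoint or the non-inferiority conclusion at 1 year. Which Tg cut-off is clinically right is not judged here.

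**What to change.** Before analysis, reconcile Secondary objectives and Oncologic secondary criteria into one set of definitions that is mutually exclusive and exhaustive, with a stated order of precedence. In that set:

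- apply the primary endpoint's Tg and antibody condition to excellent response at 3 and 5 years;
- say where unstimulated Tg above 0.2 and below 1 ng/mL falls;
- correct or confirm the phrase about stimulated Tg in the indeterminate definition;
- keep cytology and washout Tg, which the protocol triggers for suspicious lesions, as evidence for structural disease, and say how an unbiopsied lesion is classed;
- do not let category membership depend on stimulated Tg, which is not scheduled at the 1-year or annual visits; report it descriptively.

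The sponsor decides which cut-off applies. The cost is wording in the protocol and analysis plan, with ethics committee approval if made as a protocol amendment. No new visits, tests or patients are needed, because the categories can be derived from data already planned for collection.
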